### Exposure variables

–Number of days with propofol therapy preceding transition day from one clinical state to another (numeric variable), irrespective of whether a patient had propofol on transition day or not (for definition of state transitions see Figure 1)–The cumulated amount of propofol-associated energy intake (kcal/kg) (numeric variable) preceding transition day, irrespective of whether a patient had propofol on transition day or not–The amount of daily propofol-associated energy intake (kcal/kg and day) on transition day (numeric variable)–The amount of daily propofol-associated energy intake (kcal/kg and day) (categorized variable) during different phases after ICU admission. The associations of daily propofol-associated energy intake with the outcome will be cumulated for the early phase (Days 0 - 4 after ICU admission) and the late phase (Days 5 - 11 after ICU admission).

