### Statistical analysis plan

#### Descriptive analysis

Continuous variables are described by mean, SD, median, minimum, and maximum values. In addition, two-sided 95%CIs are calculated for continuous variables. Additional descriptive statistics may be calculated as needed (e.g., quartiles, coefficient of variation, etc.). In particular, the median and interquartile range (IQR) are used to describe non-normally distributed data. Frequencies and corresponding percentages per class level describe categorical variables. Patients with missing data will be excluded. However, we will examine where and how frequently missing values occur in the data overall, how often they co-occur across variables, and whether there are notable patterns of missingness across groups. We will then derive possible limitations of this study from that analysis.

For the competing risk analyses (time-to-discharge alive, time to in-hospital death), we will classify daily propofol-associated energy intake using three thresholds that define three different levels based on the amount of propofol-associated energy received. The identification of specific energy thresholds will be based on clinical practice:^(18,19)^ level I: < 1.0kcal propofol-associated energy/kg per day; level II: 1.5 - 4.5kcal propofol-associated energy/kg per day; level III: > 4.5kcal propofol-associated energy/kg per day). Suppose there is a highly uneven distribution of patient days with a given level of propofol-associated energy intake. In that case, energy thresholds may be redefined after preliminary exploratory analysis of these data, but before assessing the association with outcome.

For converting propofol-associated energy intake into mg propofol, we will assume that the use of 1% and 2% propofol in the present study was similar to that in the multinational EuroPN study on medical nutrition therapy (2% propofol: 62%, 1% propofol: 37%, unknown: 1%; unpublished observations of the EuroPN study).^(20)^ From these data, it is possible to convert propofol-associated energy intake into mg propofol. According to Appendix A, the energy levels above would roughly correspond to the following propofol dose levels: level I: < 20mg/kg per day; level II: 20 - 60mg/kg per day; level III: > 60mg/kg per day. These propofol categories, however, will only be used to interpret results. For all statistical analyses, we will use the levels defined above based on propofol-associated energy intake.

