Hazard ratios can be used to describe the association of covariates and exposures with each transition (e.g., from alive to death in the ICU). In multistate settings, separate hazards are estimated for each possible transition. These individual transition hazards are then combined to obtain the overall transition probabilities by calculating the empirical transition matrix. While hazard ratios describe the direct effect on the instantaneous risk of a transition (relative risk), transition probabilities depend on the hazards of all possible transitions (absolute risk). Together, these two quantities provide a comprehensive interpretation of the underlying processes.

A particular focus will be on the concomitant use of MV, which is one of the main reasons for propofol use in critically ill patients and therefore the most important confounder of propofol-associated outcomes. The time-dependent confounder MV is considered as a separate state^(27)^ in the multistate model (Figure 1). This has the advantage that the transitions to the absorbing states "ICU discharge alive" and "in-ICU-death", and thus the transition probabilities to these states, can be modelled separately, depending on the current time-dependent propofol status (yes or no), but also on the subject-specific history of MV treatment and propofol administration (number of days with propofol therapy, cumulated propofol-associated energy intake). As the model is conditional on propofol status at any given time, but the frequency of MV use may vary between subjects within each propofol state, it allows the association of propofol and MV status with outcomes to be disentangled.

Results for the association between the exposure variables preceding transition (number of days with propofol therapy, cumulated propofol-associated energy intake (kcal/kg), propofol-associated energy intake (kcal/kg day) on transition day), and transition risk will be presented as adjusted hazard ratios (with 95%CIs) and adjusted transition probabilities (with 95%CIs) depending on a specific day after ICU admission (Days 1 to 11).

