### Sensitivity analyses accounting for palliative care bias/confounding by indication

To account for palliative care bias in the multistate models and analysis of time-to-discharge alive/in-hospital death, a sensitivity analysis is required concerning patients with an early death after termination or beginning of propofol therapy (< 48 hours after the last day of propofol therapy). Palliative care bias arises if physicians modify therapy not for medical reasons but because of end-of-life decisions. Several scenarios are possible (Table 2):

**Table 2 t2:** Survey of sensitivity analyses that account for bias relating to indications and palliative care

	Primary outcome	Secondary outcome		
Outcome measures	Time-to-discharge-alive/in-hospital death	Hazard of state transition		
Exposure variables	Categorized daily propofol-associated energy intake (kcal/kg and day)	Number of days with propofol therapy preceding transition day	Cumulated amount of PAEI (kcal/kg) before state transition (initial state: propofol "yes")	Amount of daily PAEI (kcal/kg and day) on transition day (initial state: propofol "yes")
Sensitivity analyses	Use of a lag time of two days after the last day of propofol therapy	Re-definition of the absorbing state "in-ICU death" into "palliative in-ICU death" (for time courses of different daily states #1 to #9, Table 3) and "non-palliative in-ICU death" (all other state time series)	Re-definition of the absorbing state "in-ICU death" into "palliative in-ICU death" (if [PAEI on transition day minus PAEI on the day before transition day]/PAEI on the day before transition day ≥ 100%) and "non-palliative in-ICU death" (all other changes)	Re-definition of the absorbing state "in-ICU death" into "palliative in-ICU death" (if PAEI on transition day > 4.5kcal/kg day) and "non-palliative in-ICU death" (all other intake)

PAEI - propofol-associated energy intake; ICU - intensive care unit.

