If it is decided to either terminate supporting therapies or, based on the presumed wishes of the patient (e.g., communicated by a surrogate) or on an advance directive, not to start or to increase life-sustaining therapies (e.g., oxygen supply), propofol may be started for sedation. Death usually occurs one to two days after these therapeutic changes. To account for this bias within the transition from the state "propofol: no" to the absorbing state "propofol: yes", we will re-classify the subsequent absorbing state "in-ICU death" into "palliative in-ICU death", if death occurs one or two days after the preceding state transition (time course of states # 8 - 9, Table 3), and into "non-palliative death" in all other time courses of states.

For the reasons described in b), the preexisting propofol dose can be increased acutely to relieve symptoms. Therefore, when analyzing transitions to the absorbing ‘in-ICU death’ state in the combination with a certain preceding propofol-associated energy intake in the initial state, we will re-define the absorbing state "in-ICU death" into "palliative in-ICU death", if there is a significant increase of propofol-associated energy intake from one day to the other ([propofol-associated energy intake on transition day minus energy intake on the day before transition day]/energy intake on the day before transition day = > 100%), or if propofol-associated energy intake on transition day is > 4.5kcal/kg day, and into "non-palliative death" with all other changes/intake.

Consequently, depending on each patient's history, these sensitivity analyses will increase the number of possible state transitions (Figure 2) compared to the primary analysis (Figure 1).

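### In the sensitivity analysis of transition-day propofol intake, the type of ICU death is defined by that same intake, so non-palliative death above 4.5 kcal/kg cannot occur

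*Protocol article*

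**What the plan says.** The section Exposure variables lists, for the multistate models, "The amount of daily propofol-associated energy intake (kcal/kg and day) on transition day (numeric variable". Overall design of the multistate models confirms that this is a reported result: the association between "propofol-associated energy intake (kcal/kg day) on transition day), and transition risk will be presented as adjusted hazard ratios", together with transition probabilities.

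Table 2 gives each exposure its own check for palliative-care bias. In the last column, for intake on the transition day, the absorbing state in-ICU death is split. It is palliative "if PAEI on transition day > 4.5kcal/kg day" and non-palliative for any other intake. No further sign of end-of-life care is required.

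Sensitivity analysis for the multistate models repeats the rule, "if propofol-associated energy intake on transition day is > 4.5kcal/kg day", and joins it by an 'or' to a second rule that applies "if there is a significant increase of propofol-associated energy intake from one day to the other", meaning a relative rise of at least 100%. Deaths "with all other changes/intake" are non-palliative. Table 2, in contrast, assigns the rise rule to cumulated intake only and the 4.5 rule to transition-day intake only.

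The other two columns of Table 2 work differently. The number-of-days exposure uses the state sequences of Table 3, and the primary outcome uses a two-day lag.

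**The concern.** A check for palliative bias should separate deaths by evidence that does not depend on the exposure being tested. Here the separating evidence is the exposure. Patients above 4.5 kcal/kg still contribute time at risk, but none of their deaths can count as non-palliative. The contrast meant to be free of palliative bias therefore contains no deaths at the top of the dose range.

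The article aims to provide evidence on safe dosing, and its Limitations section relies on these sensitivity analyses to reduce end-of-life bias. For this exposure, Table 2 lists no other check. A reader who saw a hazard ratio below 1 for non-palliative death could take it as reassurance, although the labelling rule alone would produce it.

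**Working it through.** **1. Where the cut lies.** Appendix A converts kcal to mg by 1 / [1.8 × 1.1 / (2.8 × 20) + 1.1 / (2.8 × 10)] = 13.4 mg per kcal (stated: 13.5). So 4.5 kcal/kg is 4.5 × 13.4 = 60.3 mg/kg per day, which reproduces the stated boundary of about 60. The Introduction gives a maximum application rate of 95 to 120 mg/kg per day, and 60.3/120 = 50% and 60.3/95 = 63%. The relabelled range therefore starts well inside the doses that the study sets out to examine.

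**2. The logic, without any assumption.** Let h(x) be the true ICU-death hazard at transition-day intake x. The rule gives

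- non-palliative hazard: h(x) if x ≤ 4.5, and 0 if x > 4.5;
- palliative hazard: 0 if x ≤ 4.5, and h(x) if x > 4.5.

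For any x₁ > 4.5 and x₀ ≤ 4.5, the non-palliative hazard ratio is 0 / h(x₀) = 0, and the palliative ratio is h(x₁) / 0, which is undefined. Neither depends on h. If x₀ and x₁ are both at or below 4.5, the non-palliative ratio is h(x₁) / h(x₀), the true value.

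**3. Illustration with assumed inputs.** The article gives neither the distribution of intake nor a daily death risk. Assume 400,000 patient-days, gamma intake with mean 2.8 kcal/kg (shape 2, scale 1.4; 17% of days above 4.5) and a death risk of 0.02 × HR^(x − 2.8) per day. Fit a Poisson model with log-linear intake:

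| True HR per kcal/kg | All ICU deaths | Non-palliative | Palliative | Non-palliative deaths above 4.5 / all deaths above 4.5 |
|---|---|---|---|---|
| 0.90 | 0.90 | 0.74 | 1.45 | 0 / 969 |
| 1.00 | 1.00 | 0.79 | 1.47 | 0 / 1,369 |
| 1.10 | 1.09 | 0.83 | 1.49 | 0 / 1,823 |
| 1.25 | 1.25 | 0.89 | 1.52 | 0 / 3,207 |
| 1.50 | 1.43 | 0.96 | 1.57 | 0 / 7,207 |

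**4. Dependence on the share of days above 4.5.** With a true HR of 1.00, gamma intake with 2.4%, 8.5%, 17% and 34% of days above the cut gave non-palliative HRs of 0.92, 0.84, 0.79 and 0.71.

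For log-normal intake with log-SD 0.6, the share is 1 − Φ(ln(4.5/median)/0.6). The large-sample values of the same log-linear fit, with the 2% daily risk set at mean intake, are:

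| Median (kcal/kg) | Share above 4.5 | True HR 1.00 becomes | True HR 1.20 becomes |
|---|---|---|---|
| 1.5 | 3.4% | 0.89 | 1.01 |
| 2.0 | 8.8% | 0.83 | 0.92 |
| 2.5 | 16.4% | 0.77 | 0.84 |

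The estimate is below the true value in every case. Whether a true harm crosses 1 depends on the share.

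**5. The rise rule.** Table 2 applies it to cumulated intake, which Exposure variables defines as intake before the transition day. The exposure does not contain transition-day intake, so no zero is forced. Simulations with log-normal intake (median 2.5, log-SD 0.6) correlated from day to day turned a true HR of 1.00 per cumulated kcal/kg into 1.002 to 1.008.

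**The case against.** The best defence is one of scope. Table 2 holds four sensitivity analyses, and the structural zero affects one of them, for one of three exposures of the secondary outcome. The main multistate model keeps in-ICU death undivided, so an all-cause result for the same exposure will stand beside it. This is correct and limits the importance of the point.

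A second defence is that the plan uses piecewise exponential additive mixed models, which allow non-linear effects. A flexible curve would drop at 4.5 but could stay informative below it. Restricting the log-normal simulation (median 2.5) to intake at or below 4.5 recovered 1.00, 1.09 and 1.21 for true values of 1.00, 1.10 and 1.20. This also stands: the distortion belongs to contrasts that reach across or above the cut, and a flexible fit does not repair those.

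Several stronger readings are tempting but not supported:

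- *The top dose group has no non-palliative deaths.* The boundary "level III: > 4.5kcal propofol-associated energy/kg per day" belongs to the competing-risk analyses. The multistate exposure is numeric, so there is no such group here.
- *Harm is bound to appear as benefit.* The downward bias is certain for contrasts across the cut, but a change of sign is not. With 3.4% of days above the cut, a true 1.20 became 1.01.
- *The rise rule has the same fault.* It forces no zero, and its simulated bias was negligible and not towards safety.
- *The rise rule divides by zero.* The text introduces it for an existing dose that is increased, so prior-day intake is presupposed. What remains is a gap in wording for patients who have just started propofol.

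**Conclusion.** The rule is wrong as written for the sensitivity analysis of transition-day intake and should be changed before analysis. That no non-palliative death can occur above 4.5 kcal/kg, and no palliative death at or below it, follows from the wording alone. The direction of the bias, towards apparent safety for non-palliative death at high intake and apparent harm for palliative death, follows with it.

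The size is not known. It rests on an assumed intake distribution, an assumed 2% daily death risk and a log-linear fit. A true HR of 1.00 became 0.92 to 0.71 as the share of days above the cut went from 2.4% to 34%.

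A reader might infer that the study's main conclusions on propofol safety are compromised. They are not: the primary competing-risk analysis, the number-of-days analysis and the main multistate model do not use this rule.

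**What to change.** For transition-day intake, delete the 4.5 rule from the last column of Table 2 and from the text as a definition of death type. Keep all in-ICU deaths as one absorbing state and lag the exposure by two days, using intake up to two days before the transition day. This is in line with the two-day lag planned for time to discharge alive and in-hospital death. It also fits the article's own statement that death usually follows one to two days after an end-of-life change in therapy.

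The state sequences of Table 3 would not be an adequate substitute. The intake analyses start from a propofol-yes state, and only courses 8 and 9 have such an initial state. Both are without mechanical ventilation, so ventilated patients dying on propofol would never be classed as palliative.

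Two wording changes belong with this. Align the text, which joins the two rules by 'or', with Table 2, which assigns the rise rule to cumulated intake only. State that the rise rule applies only when intake on the day before is above 0.

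The cost is the last two days of exposure information before each transition, and the early transitions that have no lagged value. No new data are needed.

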**Figure 2 f2:**
[figure not shown]
Modified multistate model describing the transitions between different clinical states depending on the risk of a palliative care bias.

### Sensitivity analysis for the competing risk models used to analyze time-to-discharge alive/in-hospital death

When analyzing the cumulative association between propofol-associated energy intake and these outcomes, we will use a lag time of two days to minimize indication bias due to lower doses approaching discharge (or to higher doses before death). Consequently, the time window (defined by the lead time, see above) for which cumulated associations of propofol-associated energy intake with time-to-discharge alive/in-hospital death are calculated will be shortened by two days.

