### Selection of the study population

#### Inclusion criteria

Patients selected from the database will be aged 18 years or over and have a body mass index (BMI) of over 13kg/m^2^. Other inclusion criteria will be an ICU length-of-stay (LOS) of > 48 hours. The rationale behind this inclusion criterion is that the potentially detrimental effects of propofol on survival are not attributable to immediate or acute reactions, but instead require more than 48 hours of therapy to manifest (e.g., in the event of propofol infusion syndrome).^(1,14)^

For patients admitted to the same unit during the same hospital stay, we will only analyze the first ICU admission. Patients readmitted after hospital discharge will be included as separate cases.

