### Outcome measures

–**Primary outcomes:** time-to-hospital discharge-alive as a surrogate of morbidity, and to in-hospital death (adjusted hazard ratios and 95% confidence intervals [95%CI]).Adjusted hazard ratios compare two levels of daily propofol-associated energy intake. They will be calculated separately for each day after ICU admission using sub-distributional and cause-specific hazard models. The observation period will start on the day of ICU admission, and events (day of discharge alive/in-hospital death) will be registered from day 2 after ICU admission until the end of the lead-time (defined as twice the number of days that a patient received propofol therapy).–**Secondary outcomes:** the risk of state transition (adjusted hazard ratio and 95%CI) and the transition probabilities between the different states (Figure 1).State transition risks and probabilities will be referred to a certain amount of propofol-associated energy intake or a specific duration of propofol therapy; adjusted hazard ratios will be calculated for all 17 transitions (Figure 1). State transition will be registered until day 13 after ICU admission. Initial and absorbing states include "propofol: no/MV: no", "propofol: yes/MV: no", "propofol: no/MV: yes", "propofol: yes/MV: yes", post-transition absorbing states include "in-ICU death" and "ICU discharge alive.

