### Overall design of the competing risk models used to analyze time to discharge alive and to in-hospital death

The primary aim will be to analyze the association between daily propofol-associated energy intake from day 1 to day 11 after ICU admission and the time to the hospital endpoint (discharge alive with in-hospital death as a competing risk).

Recording of propofol-associated energy intake was stopped if a patient died, was discharged from the ICU, or was in the ICU for more than 11 days. However, our statistical model requires information on propofol-associated energy intake on propofol days 1 to 11 after ICU admission for all surviving patients, even if patients were discharged from the ICU before day 11. Assuming no propofol-associated energy intake after ICU discharge alive, we will impute a daily propofol-associated energy intake of 0 for these patients.

To account for the fact that a short duration of propofol therapy (and propofol-associated energy intake) may not affect outcome over a more extended period, we will use a lead-time defined as twice the number of days that a patient received propofol therapy. These lead times provide a window in which propofol-associated energy intake on a given day could have affected the subsequent day of discharge alive (time to discharge alive).

To facilitate the interpretation of the associations between propofol-associated energy intake and outcome estimated by our model, we will construct five different hypothetical propofol-associated energy intake use patterns (reflecting three different levels of daily propofol-associated energy intake (low, medium, high) on propofol days 1 to 11). These levels of use will also be used to model associations between propofol-associated energy intake and outcomes. Similar to our recent publications,^(9,15)^ we will distinguish between an early (days on propofol #0 to #4) and a late (days on propofol #5 to #11) acute phase.

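### The primary competing-risk models apply no lag although the plan expects intake to shift before events, and the lagged check also changes which events are counted

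*Protocol article*

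**What the plan says.** The section on the overall design of the competing risk models sets the time frame of the primary analysis: "we will use a lead-time defined as twice the number of days that a patient received propofol therapy". It gives the purpose as follows: "These lead times provide a window in which propofol-associated energy intake on a given day could have affected the subsequent day of discharge alive". No lag is mentioned there.

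The same quantity limits event counting. Under Outcome measures, discharges and deaths "will be registered from day 2 after ICU admission until the end of the lead-time (defined as twice the number of days" on propofol. The competing-risk design section says that the lead matrix sets when events are recorded, and that the cumulative incidence runs to the end of the lead time.

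The lag appears only as a sensitivity analysis. The section on sensitivity analysis for the competing risk models states: "we will use a lag time of two days to minimize indication bias due to lower doses approaching discharge", and adds higher doses before death in brackets. The consequence given is that the window for which cumulated associations "are calculated will be shortened by two days". Table 2 places the two days after the last propofol day. Limitations describes the lag as excluding events close to that day, and rates confounding by indication as highly relevant.

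**The concern.** If clinicians reduce propofol as a patient nears discharge, low intake in the last days is partly a result of approaching discharge. A model that lets those days act on the hazard at once can show an association with no effect behind it. The plan recognises this mechanism but leaves the primary hazard ratios exposed to it.

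The lagged analysis is meant to show how much this matters. It can do so only if the lag is the one thing that changes. Here the lag also shortens a window that decides which events count. If the two results differ, the reader cannot tell whether bias was removed or different events were analysed. If they agree, that reassures less than it should. The study aims to inform safe dosing and duration, so the comparison carries real weight.

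**Working it through.** **Inputs, all from the protocol article.** Lead time = 2n days (competing-risk design; Outcome measures). Lag = 2 days, with the window shortened by the same amount (sensitivity analysis for the competing risk models). Events counted from day 2 after ICU admission (Outcome measures). Inclusion requires an ICU stay above 48 hours and no minimum number of propofol days, so n = 1 is eligible.

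**Step 1: window length.** Primary window = 2n. Lagged window = 2n − 2. Share of the primary window within two days of exposure = 2/(2n) = 1/n.

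| n | Primary | Lagged | Share within first two days |
|---|---|---|---|
| 1 | 2 | 0 | 100% |
| 2 | 4 | 2 | 50% |
| 3 | 6 | 4 | 33% |
| 5 | 10 | 8 | 20% |
| 11 | 22 | 20 | 9% |

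For scale only, Limitations cites a median sedation time of 2.6 days in a randomized study, where the share would be 1/2.6 = 38%. The article gives no distribution of n for this database.

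**Step 2: which days remain.** The article does not fix the clock or the treatment of interval ends, so each reading is shown.

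- Counted from exposure, first day excluded: n = 1 goes from days 1–2 to none; n = 2 from days 1–4 to 3–4; n = 3 from days 1–6 to 3–6.
- Counted from exposure, both ends included: n = 1 goes from days 0–2 to day 2 alone.
- Counted from admission, with events from day 2 and two days taken off the end: n = 1 goes from day 2 to none; n = 2 from days 2–4 to day 2; n = 3 from days 2–6 to 2–4.

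On the admission clock the cut removes late events and leaves the most recent intake in place, which is not what a lag is for. Starting event counting at day 2 gives day-0 intake a two-day gap in the primary model, but intake on later days has none.

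**Step 3: the lag as described in three places.**

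- Table 2: two days following the last propofol day.
- Sensitivity analysis section: the window "will be shortened by two days", with no statement of which end is cut.
- Limitations: events near the last propofol day are excluded.

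The first and third are anchored to the end of therapy, the second to each day's effect window. They give different data sets.

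**Step 4: direction.** For discharge, the article names one mechanism, lower doses as discharge approaches, which would make higher intake look as if it delays discharge. For death it names several. The multistate sensitivity section describes propofol being replaced by other drugs one to two days before death, and seven of the nine sequences in Table 3 are propofol stopping. It also describes propofol being started or increased before death. These act in opposite directions.

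**Step 5: size.** The shift in intake before events is not reported, so any hazard ratio rests on an assumption. Null simulations of 18,000 patients, assuming 20% less intake in the two days before discharge and 20% more before death, gave unlagged hazard ratios of 0.75 (discharge) and 1.19 (death) under one design, and 0.60 and 1.55 under another. Lagged values were 0.99 to 1.00. With a 50% shift the first design gave 0.29 and 1.31. These show the mechanism only. The shift was placed in exactly the two days that the lag removes, so the lagged null result is built in.

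**The case against.** The strongest reply is that the plan names the bias, pre-specifies a lagged analysis and discloses the issue in Limitations. An unlagged primary model with a lagged sensitivity analysis is a defensible order, and both results will be reported. That stands as far as order goes, which is why promoting the lagged model is the more debatable part of the fix. It does not answer the change in events between the two models.

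A second reply is that the shortened window is only an effect window: patients stay in the risk set and recent intake contributes nothing. The sensitivity section can be read that way. Outcome measures and the competing-risk design section, however, tie the lead time to event recording, and Limitations speaks of excluded events. The text does not settle it in favour of the milder reading.

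Third, on the admission clock a one-day patient has only day 2 in the primary model. That near-empty window comes from the 2n rule itself, which is a separate matter. The number of one-day patients is also not given.

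Two stronger readings are tempting and should not be drawn:

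- A reader might take the inclusion rationale, that harmful effects "require more than 48 hours of therapy to manifest", as a delay after each dose, so that the last 48 hours of intake can have no effect. It concerns duration of therapy and is used to justify the length-of-stay criterion. It says nothing about recent intake in a patient already on propofol for a week.
- A reader might infer that the primary hazard ratios for death are biased towards harm. Step 4 shows that the article describes mechanisms in both directions.

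Nor do the simulated ratios estimate anything in this database. The first design's ratios are per 1 kcal/kg, whereas the planned exposure is in three categories. The endpoint is hospital discharge, with intake set to zero after ICU discharge alive.

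**Conclusion.** The point holds in this form. The primary competing-risk models include, without a lag, the days on which the article itself expects intake to shift. The one check on this shortens the window from 2n to 2n − 2 days, which is 0 for n = 1 and half the original length for n = 2. Because the lead time is also tied to event recording, the lagged and unlagged analyses differ in events as well as in lag, and the three descriptions of the lag do not agree.

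This rests on reading the lead time as governing event counting, as Outcome measures states. Under a closed count from exposure, one-day patients keep a single boundary day. The direction of bias is plausible for discharge and open for death. Neither its size nor the number of patients affected can be derived from the document. It should be corrected before the models are fitted.

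**What to change.** 1. Define the lag once and reconcile Table 2, the sensitivity analysis section and Limitations with it. Intake on day t enters the hazard only from day t+2, and its effect window is moved to [t+2, t+2+2n] rather than cut. The length stays 2n: measured from the exposure day, n = 1 gives days 2 to 4, n = 2 days 2 to 6 and n = 3 days 2 to 8. State whether interval ends are included.
2. Fix the risk set and the last event-counting day separately from the effect window, and use the same ones in both models. Moving the start while tying the end to the old lead time would still shorten the window. The existing 60-day follow-up leaves room: with t = 11 and n = 12 (days 0 to 11), the latest window ends at 11 + 2 + 24 = day 37. State how patients with n = 0 or 1 are handled.
3. Report the lagged model as primary or co-primary beside the unlagged one.

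Both models are already planned, so the work is a change to the lag-lead matrix, a common event-counting rule and edits to the text. The price is slightly wider intervals and no information from the lagged model on effects within two days of exposure.
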